## Abstract

**Background:**

Acute myocardial infarction (AMI) remains a leading cause of mortality worldwide, with substantial variation across populations shaped by environmental conditions, geographic context, and healthcare accessibility. However, current risk assessment approaches based on baseline measurements may not adequately capture short-term risk or population heterogeneity.

**Methods and analysis:**

This multicentre prospective cohort study will recruit 2,340 adults aged 20–85 years with an estimated 10-year atherosclerotic cardiovascular disease risk ≥20%. Participants will be enrolled from five hospitals in Gansu Province, China, representing variation in ethnicity, altitude, and healthcare access, including Han, Hui, Tibetan, and Kazakh populations. Baseline assessments will include standardized questionnaires, clinical evaluation, and cardiometabolic profiling. Participants will be followed every 3 months for 24 months, with repeated measurements of behavioral, physiological, and biomarker indicators, including wearable electrocardiographic monitoring. Environmental exposures and healthcare accessibility will be assigned using geospatial data. The primary outcome is first incident AMI. Time-to-event models with time-varying variables will be used to examine how within-individual changes in risk indicators are associated with AMI across environmental and ethnic contexts.

**Ethics and dissemination:**

The study has been approved by the Ethics Committee of Gansu Provincial Hospital. Written informed consent will be obtained from all participants. Findings will be disseminated through peer-reviewed publications and scientific presentations.

**Clinical trial registration:**

ChiCTR2500104518.

## Introduction

Acute myocardial infarction (AMI) remains a leading cause of mortality worldwide and reflects a major burden of cardiovascular disease at the population level (1). Beyond individual risk factors, environmental conditions and healthcare accessibility play an important role in shaping cardiovascular outcomes. Regional variation in air pollution, climate, altitude, and healthcare resources contributes to differences in cardiovascular risk, highlighting the importance of contextual determinants in public health (2–4).

Ethnic differences further contribute to heterogeneity in cardiovascular risk. Variations in lifestyle, dietary patterns, and social conditions across ethnic groups have been associated with differences in cardiovascular risk profiles and disease burden (5, 6). In western China, populations including Han, Hui, Tibetan, and Kazakh communities are exposed to distinct environmental and social contexts, resulting in heterogeneous cardiometabolic risk patterns (7–9). High-altitude exposure in Tibetan populations is associated with specific physiological adaptations that may influence cardiovascular risk (10).

Despite these insights, most existing studies have focused on long-term risk estimation or cross-sectional comparisons. Commonly used tools, such as the Framingham Risk Score and the China-PAR model, are based on baseline measurements and assume relatively stable risk over time (11–13). Although recent studies have incorporated longitudinal data and time-varying models (14, 15), environmental exposure, healthcare accessibility, and ethnic context are rarely examined simultaneously. As a result, it remains unclear whether short-term risk patterns preceding first AMI differ across populations.

To address this gap, a prospective study integrating environmental exposure, ethnic background, healthcare accessibility, and repeated multidimensional assessment is needed. The present study aims to investigate the short-term risk of first AMI in a multiethnic cohort and to examine how environmental and ethnic differences are associated with variation in short-term cardiovascular risk. By focusing on population-level heterogeneity and within-individual changes over time, this study seeks to provide a more context-sensitive understanding of cardiovascular risk and to inform targeted prevention strategies.

## Method

### Study design

This is a prospective, multicentre, hospital-based cohort study with an embedded nested case–control component conducted across five hospitals in Gansu Province, China (Figure 1). Gansu Province, located in northwestern China (16), provides substantial variation in altitude, ethnicity, environmental exposure, and healthcare accessibility. The study aims to examine variation in short-term risk of AMI across populations exposed to different environmental, geographic, and healthcare conditions in western China. Participating centers include Gansu Provincial Hospital (103°51′E, 36°03′N,predominantly Han population; mean altitude 2,098 m), Aksai Kazakh Autonomous County Hospital (94°20’E, 39°24’N, predominantly Kazakh; 3,289 m), Dingxi People’s Hospital (104°37’E, 35°34’N, predominantly Han; 2,282 m), Linxia People’s Hospital (103°14’E, 35°36’N, predominantly Hui, 2,255 m), and Gannan People’s Hospital (102°91’E, 34°98’N, predominantly Tibetan, 3,369 m). These centers represent distinct combinations of altitude, ethnicity, and healthcare accessibility. Standardized protocols are applied across all sites for recruitment, baseline assessment, follow-up, and outcome adjudication, with centralized coordination and regular cross-site training to ensure consistency.

**Figure 1 fig1:**
[figure not shown]
Overview of the study area and environmental determinants. **(A)** Inset map indicating the geographic position of Gansu Province within China. **(B)** Map of Gansu Province showing the locations of the five participating hospitals and the predominant ethnic groups (Han, Hui, Tibetan, Kazakh, Others) with their respective percentages at each site. **(C)** Spatial distribution of elevation (m) across Gansu. **(D)** Spatial distribution of annual mean temperature (°C) across Gansu. **(E)** Spatial distribution of PM2.5 concentration (μg/m³) across Gansu. **(F)** Spatial distribution of hospital accessibility index.

### Study population

A total of approximately 2,340 adults will be enrolled from five participating centers, representing Han, Hui, Tibetan, and Kazakh populations across regions with varying altitude, environmental exposure, and healthcare accessibility. Recruitment targets are prespecified according to catchment characteristics, with planned enrolment of 900–1,050 Han, 650–750 Hui, 400–500 Tibetan, and 250–350 Kazakh participants. Sample size estimation is based on an event-driven approach (Supplementary Material 1). Assuming a 4% cumulative incidence of first AMI over 24 months, approximately 80 events are expected, supporting multivariable modeling and subgroup analyses.

Participants will be eligible if they: (1) are aged 30–85 years; (2) have an estimated 10-year atherosclerotic cardiovascular disease (ASCVD) risk ≥20% (6); (3) are permanent residents of the study area (≥6 months per year); (4) provide written informed consent; and (5) agree to repeated follow-up and biospecimen collection. Exclusion criteria include: (1) major comorbid conditions such as end-stage renal disease, hepatic failure, or active malignancy; (2) acute illness at enrolment; (3) severe psychiatric disorders; (4) substance abuse; and (5) pregnancy or breastfeeding (17). Loss to follow-up is defined as absence from more than two scheduled visits or permanent discontinuation. Follow-up will be maintained through clinic visits supplemented by telephone or electronic contact where necessary.

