Baseline assessment: The project will be carried out from 2025 to 2027 in Gansu Provincial People’s Hospital, Aksay County People’s Hospital, Linxia Prefecture People’s Hospital, Gannan Tibetan Autonomous Prefecture People’s Hospital, and Dingxi City People’s Hospital. High-risk cardiovascular patients of the Han, Hui, Tibetan, and Kazakh ethnic groups will be identified through cardiovascular outpatient clinics, community screening programs, and electronic medical record systems. Follow-Up: it will be conducted at 3, 6, 9, 12, 15, 18, 21, and 24 months after enrollment in the cohort, for a period of 2 years. *Standardized assessment: Demographics, lifestyle, psychology, diet, and medication adherence questionnaires. +Sociodemographic characteristics: Age, sex, ethnicity, residence type, education, occupation, and income. ++Lifestyle factors: Smoking, alcohol consumption, dietary habits, physical activity, and sleep quality. †Clinical history: Hypertension, diabetes, dyslipidemia, previous stroke or TIA, family history of coronary heart disease, and history of drug use. ‡Anthropometry and physiological parameters: Including height, weight, BMI, waist circumference, blood pressure and body fat percentage. **Fasting venous blood tests: High-sensitivity C-reactive protein (hs-CRP), high-sensitivity troponin I (hs-TnI), creatine kinase (CK), creatine kinase-MB (CK-MB), lactate dehydrogenase (LDH), aspartate aminotransferase (AST), soluble suppression of tumorigenicity 2 (sST2), N-terminal pro–B-type natriuretic peptide (NT-proBNP), lipoprotein-associated phospholipase A2 (Lp-PLA2), fasting glucose, insulin, hemoglobin A1c (HbA1c), and a full lipid panel (total cholesterol, low-density lipoprotein cholesterol(LDL-C), high-density lipoprotein cholesterol (HDL-C), and triglycerides. ¶72-h wearable electrocardiogram (ECG) monitoring: A validated clinical-grade device (Shanghai Yishi Technology Co., Ltd.) will be used to continuously conduct 72-h wearable ECG and heart rate variability (HRV) monitoring. The data will be transmitted in real-time to a secure cloud platform, and the NARON CardioAI system will be used for automatic analysis, waveform classification, and feature extractio. ¶¶Transthoracic echocardiography: Unless there are other clinical indications, an echocardiogram will be performed once a year to evaluate the left ventricular ejection fraction and the situation of abnormal wall motion. ***Coronary computed tomography angiography (CCTA): If there are clinical indications should be repeated every 12 months. Assessment Tools: Includes the Rose Angina Questionnaire, The Canadian Cardiovascular Society Angina Classification, The Patient Health Questionnaire-9 (PHQ-9), The Generalized Anxiety Disorder-7 (GAD-7), The Perceived Stress Scale - 10 (PSS-10), The Pittsburgh Sleep Quality Index (PSQI), The Semi-quantitative Food Frequency Questionnaire (FFQ), The International Physical Activity Questionnaire Short Form (IPAQ-SF), The General Medication Adherence Scale (GMAS).

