#### Environmental and contextual data

Environmental variables, comprising monthly averaged meteorological parameters and air pollutant concentrations, were assigned to each patient according to their residential location and the date of hospital admission. Meteorological metrics, such as temperature, precipitation and relative humidity, were acquired from the ECMWF Reanalysis v5 (ERA5) product, which offers global coverage at a 0.25° × 0.25° gridded resolution (approximately 25 km at the equator) (3). For air pollution exposure assessment, concentrations of fine particulate matter (PM2.5 and PM10) (31), ozone (O3) (32), and nitrogen dioxide (NO₂) (33) were derived from the China High-Resolution and High-Quality Near-Surface Air Pollutants (CHAP) Dataset, which provides estimates at a high spatial resolution of 1 km. Elevation above sea level was also incorporated to account for its potential influence on AMI risk across different altitudes.

Healthcare access indicators include average travel time to the nearest secondary or tertiary hospital, hospital bed density, and physician density per 1,000 population (33). Information on socioeconomic factors, including city-level per capita income, employment patterns, occupational classifications, educational attainment, and housing conditions, will be systematically collected during scheduled follow-up visits and cross-referenced with official statistics from the Gansu Statistical Yearbook issued by the Gansu Provincial Bureau of Statistics, China.

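### Participants may live elsewhere for up to six months a year, but weather and pollution are assigned from one residence with no update described, so months away can carry the wrong exposure (size unknown)

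*Protocol article*

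**What the plan says.** All references are to the protocol article.

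- **Study population, inclusion criterion 3:** participants "are permanent residents of the study area (≥6 months per year". No minimum number of years at the address is given.
- **Environmental and contextual data, weather and pollution:** the values are monthly averages. They "were assigned to each patient according to their residential location and the date of hospital admission". The location is singular.
- **Same section, altitude:** "Elevation above sea level was also incorporated to account for its potential influence on AMI risk across different altitudes". The sentence does not say whether elevation is that of the home or of the centre.
- **Same section, access:** "Healthcare access indicators include average travel time to the nearest secondary or tertiary hospital, hospital bed density, and physician density per 1,000 population". The place to which these are tied is not stated here. The abstract says only that access is assigned from geospatial data.
- **Table 1 footnote, baseline only:** "Sociodemographic characteristics: Age, sex, ethnicity, residence type, education, occupation, and income". Under Baseline variables, residence type means urban or rural.
- **Study design:** "These centers represent distinct combinations of altitude, ethnicity, and healthcare accessibility". The five centre altitudes run from 2,098 m to 3,369 m.
- **Outcomes:** the 90 days before AMI are singled out for the study of short-term change.

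**The concern.** The two rules do not fit together. One allows a participant to be somewhere else for half of every year. The other gives each participant the weather and pollution of one place. Nothing described in the article records when a participant is away, or where.

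This is an error of place, so getting the calendar month of exposure right would not remove it. It matters because environment, altitude and access are the contrasts on which the study is built, both in the primary Cox model and in the heterogeneity analyses. It matters most for the short-term question: a participant who is away in the weeks before an AMI would carry the wrong values in the period of greatest interest.

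**Working it through.** The article gives no figure for part-year residence, so there is no stated result to reproduce. The check has four steps.

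**1. Do the rules permit misassignment?** Time allowed away = 12 − 6 = 6 months a year. Places used for weather and pollution: one. Updates of that place described: none. Residence type at baseline is urban or rural, not an address. The housing conditions collected at follow-up visits are not described as a location either. So misassignment is permitted, and nothing described would detect it.

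**2. Scale for one person.** Only altitude has centre values in the article, so only altitude can be illustrated.
- Between-centre range: 3,369 − 2,098 = 1,271 m.
- Annual-mean error for a half-year away = 0.5 × (home altitude − away altitude).
- Home 3,369 m, away 2,098 m: 0.5 × 1,271 = 635.5 m, half the range.
- For a single month away the error is the whole difference, 1,271 m. This is the relevant form for exposures assigned by the month.
- If the second home is at a similar altitude, the error is near zero.
- If the second home is outside the study area at an assumed 0 to 1,500 m, the annual-mean error for a participant at the highest centre is 0.5 × (3,369 − 1,500) = 934.5 m up to 0.5 × 3,369 = 1,684.5 m. That is 0.74 to 1.33 of the range.

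**3. Effect on a hazard ratio.** Assumptions: a share p of high-centre participants spends half of each year at 2,098 m; movement is unrelated to AMI risk; the log hazard is linear in altitude; the relevant exposure is the annual mean; the true HR is 1.50 over the full range. The true contrast is then 1,271 × (1 − p/2), and the estimated HR is approximately exp[ln(1.50) × (1 − p/2)].

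| Assumed p | True contrast (m) | Estimated HR | Shift in log HR |
|---|---|---|---|
| 10% | 1,207 | 1.47 | 0.02 |
| 20% | 1,144 | 1.44 | 0.04 |
| 40% | 1,017 | 1.38 | 0.08 |

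**4. Comparison with sampling error.** The Tibetan and Kazakh target midpoints are 450 and 300. If these participants make up the two high centres, the high-altitude share is 750/2,340 = 0.32. With the stated 80 or so events, the standard error of a high-versus-low log HR is about 1/√(80 × 0.32 × 0.68) = 0.24. The shifts above are then under one tenth, about one sixth and about one third of a standard error.

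**The case against.** **This may be detail that a condensed article leaves out.** A six-month residence minimum contradicts nothing by itself, and address history could sit in a full protocol or questionnaire manual. That is a fair reason for restraint. But the article does fix both rules, eligibility and single-location assignment, and the point concerns how those two stated rules combine.

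**The follow-up rule may remove such people.** Absence from more than two scheduled visits counts as loss. Someone away six months a year could miss about two of four visits annually, or four of eight, and be censored. This holds only in part. The third missed visit would fall in year 2, after at least a year of follow-up. Someone away three months a year would miss about two visits in all and stay in. Telephone or electronic contact may keep others in as well.

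**The limitations section covers it.** It concedes that environmental factors are not fully captured, but as residual confounding. It does not name misassigned exposure.

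**The effect may be small.** This stands. The shares in the table are assumed, and even at 40% the computed shift is about a third of a standard error, toward the null.

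**Stronger readings the documents do not support.** A reader might infer that the error is capped at half the between-centre range. It is not: a second home need not lie at any centre's altitude, monthly values give the full difference, and no such range can be computed for climate, pollution or access. A reader might also infer that movement follows season, livelihood or ethnic group and so creates spurious ethnic differences. Nothing in the article describes who moves or where.

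**Conclusion.** The concern holds as a gap of modest and unknown size. The article allows up to six months a year away, assigns weather and pollution from one residence, and describes no update of that residence in 24 months. Exposure in months away can therefore be wrong. That any participant's exposure actually is wrong cannot be shown, because the article gives no count of part-year residents.

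For weather and pollution, the single location is stated. For altitude and access, it is an inference.

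The figures of 636 m and HR 1.47, 1.44 or 1.38 are illustrations. They depend on an assumed share of movers, an assumed destination, a half-year absence, annual-mean altitude as the exposure and a true HR of 1.50. They are neither a bound nor an estimate. The case for acting rests on the low cost of the remedy and on the difficulty of recovering residence history accurately after follow-up, not on a demonstrated large bias.

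**What to change.** 1. At enrolment, record how long the participant has lived at the current address, any second address, and the months usually spent there.
2. At each 3-monthly visit, including telephone or electronic contacts, ask where the participant has lived since the last contact.
3. Assign weather, pollutants, elevation and access as time-updated values over the places actually lived in, and state explicitly that elevation and access follow residence. The article describes the weather product as global and the pollutant dataset as covering China, so most second addresses should be within reach.
4. Prespecify a sensitivity analysis restricted to near full-year residents, for example those present at least 11 months a year and resident for at least a year before enrolment.
5. Report the number of part-year residents by centre and ethnic group, so that readers can judge the size of the problem.

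The cost is one or two questionnaire items per visit, some geocoding and one extra analysis. Eligibility and recruitment targets stay as they are.

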### Variables and data collection

#### Baseline variables

At enrolment, participants undergo standardized assessments including questionnaires, physical examination, laboratory testing, cardiovascular imaging, and physiological monitoring (Table 1; Figure 2). These measurements are designed to capture both individual-level risk factors and population-level variation related to environmental and ethnic contexts. Sociodemographic variables include age, sex, ethnicity, residence type (urban or rural), education level, occupation, and household income. Clinical history captures physician-diagnosed hypertension, diabetes mellitus, dyslipidaemia, prior stroke or transient ischemic attack (TIA), and family history of coronary artery disease (CAD), together with current medication use. Lifestyle-related variables include smoking status, classified as never, former, or current smoking, alcohol consumption, dietary patterns, physical activity level, sleep quality, medication adherence, and psychological status, which may vary across environmental and sociocultural settings. Physiological measurements include systolic blood pressure, diastolic blood pressure, resting heart rate, body mass index, waist circumference, and body fat percentage (18). Laboratory biomarkers include inflammatory and cardiac stress markers, cardiac enzymes, and metabolic indicators reflecting glucose and lipid metabolism (Supplementary material) (13, 19, 20). Cardiac imaging includes transthoracic echocardiography and coronary computed tomography angiography (CCTA) where clinically indicated. Continuous 72-h electrocardiogram (ECG) and heart rate variability (HRV) monitoring are performed at baseline using a clinically validated wearable device (ref) (Supplementary material). Data are collected using standardized procedures and processed according to predefined quality-control criteria to ensure comparability across study sites.

**Table 1 tab1:** Schedule of assessments and data collection in the AMI cohort study.

Evaluation parameters	Baseline	Follow-up							
		3 m	6 m	9 m	12 m	15 m	18 m	21 m	24 m
Informed consent	x								
Inclusion criteria met	x								
Standardized assessment*	x								
Sociodemographic characteristics+	x								
Lifestyle factors++	x								
Clinical history†	x								
Anthropometry and physiological parameters‡	x	x	x	x	x	x	x	x	x
Fasting venous blood test**	x	x	x	x	x	x	x	x	x
72-h wearable electrocardiogram monitoring¶	x		x		x		x		x

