### Outcomes

The primary outcome is first incident AMI during the 24-month follow-up period. AMI events will be adjudicated according to the Fourth Universal Definition of Myocardial Infarction (2018), based on cardiac biomarker changes together with clinical, electrocardiographic, imaging, and symptom-related evidence. This outcome is defined to capture short-term occurrence of major cardiovascular events within individuals, allowing assessment of variation in near-term risk across populations with different environmental exposures, ethnic backgrounds, and healthcare accessibility.

Secondary outcomes include longitudinal changes in physiological and biochemical indicators, healthcare utilization, and short-term variation in risk markers preceding AMI. Repeated measurements of biomarkers and physiological parameters will be used to evaluate temporal changes within individuals, particularly within the 90 days preceding AMI, to characterize short-term fluctuations in cardiovascular risk. In addition, differences in these trajectories will be examined across environmental and ethnic subgroups to assess population-level heterogeneity in risk patterns.

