## Discussion

AMI remains a leading cause of mortality worldwide, and its burden continues to be substantial in China (1, 2). Conventional tools such as the Framingham Risk Score and China-PAR are designed to estimate long-term cardiovascular risk based on baseline characteristics and are widely used in population screening (11, 13). However, these models assume relative stability of risk profiles and do not capture short-term variation preceding acute events. This limitation is particularly relevant for first incident AMI, which represents the transition from a high-risk state to overt disease before treatment and secondary prevention modify the clinical course. Recent work has highlighted the value of dynamic and time-updated cardiovascular risk assessment (14), yet evidence remains limited regarding whether short-term risk trajectories preceding first AMI differ across populations exposed to different environmental and ethnic contexts. The present study addresses this gap within a multiethnic and environmentally heterogeneous setting. Repeated assessments of behavioral, psychosocial, physiological, and biomarker indicators capture changes preceding first AMI that are not reflected by baseline risk profiles alone.

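### The primary outcome is first AMI, but no listed criterion or baseline history item covers prior MI, so recurrent infarctions can enter the analysis as first events

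*Protocol article*

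**What the plan says.** **Outcome.** The Outcomes section states: "The primary outcome is first incident AMI during the 24-month follow-up period". The Discussion explains why a first event matters: it is one "which represents the transition from a high-risk state to overt disease before treatment and secondary prevention modify the clinical course". There, first means first in the participant's life.

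**Eligibility.** The Study population section numbers five inclusion criteria. The one on cardiovascular risk is to "have an estimated 10-year atherosclerotic cardiovascular disease (ASCVD) risk ≥20" per cent. The others concern age, residence, consent, and agreement to follow-up and sampling. The five exclusions read "Exclusion criteria include: (1) major comorbid conditions such as end-stage renal disease, hepatic failure, or active malignancy; (2) acute illness at enrolment", then "3) severe psychiatric disorders; (4) substance abuse; and (5) pregnancy or breastfeeding". Prior MI and coronary disease appear in neither list.

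**Baseline history.** The Baseline variables section says: "Clinical history captures physician-diagnosed hypertension, diabetes mellitus, dyslipidaemia, prior stroke or transient ischemic attack (TIA), and family history of coronary artery disease (CAD". Drugs in use are recorded as well. The note to Table 1 gives nearly the same list: "Hypertension, diabetes, dyslipidemia, previous stroke or TIA, family history of coronary heart disease, and history of drug use".

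**Recruitment.** The note to Table 1 says that high-risk patients "will be identified through cardiovascular outpatient clinics, community screening programs, and electronic medical record systems".

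**Adjudication and analysis.** Suspected events go to an independent blinded panel that applies the Fourth Universal Definition (Follow-up assessments). The Cox model counts time from enrolment, and its named covariates do not include prior MI (Primary outcome analysis).

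**The concern.** An analysis of time to first AMI needs a risk set made up of people who have not yet had one. The printed criteria do not secure this, and the printed baseline data do not record who would violate it. One of the three recruitment routes is a setting where patients with an old infarction can be expected.

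People with a prior MI plausibly differ from the rest in their hazard of AMI, in treatment, and in troponin, NT-proBNP and wall motion, all of which the study measures. Mixing them in would blur the associations between risk indicators and first AMI. If their share differed between sites, it would also be entangled with ethnicity and altitude, because the Study design section characterises each centre by its predominant ethnic group and its altitude. The article does not say that recruitment routes differ by site, so this last effect is a possibility and not a demonstrated bias.

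**Working it through.** **Step 1. Set the passages side by side.**

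| What the endpoint needs | What the article provides |
|---|---|
| No MI before time zero | Ten numbered criteria, none mentioning MI or coronary disease |
| A record of MI status at baseline | Two history lists: own stroke or TIA and family coronary disease, but no own MI, coronary disease or revascularisation |
| A check that an event is the first | Adjudication of whether an AMI occurred; no described step on whether it is the first |
| Adjustment or restriction if prevalent cases are admitted | No prior-MI term among the named covariates; no stated restriction |

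The gap is the same in all four places.

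**Step 2. The plan's own event figure.** Inputs from the Study population section: about 2,340 participants, 4% cumulative incidence of first AMI over 24 months, about 80 events.

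- 2,340 × 0.04 = 93.6, which is not 80.
- With an assumed 15% loss: 2,340 × 0.85 × 0.04 = 79.6, which agrees with 80.

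The article states no loss rate, and the derivation is in supplementary material not shown, so 80 is not called wrong here. The present point does not depend on it.

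**Step 3. Share of recurrent events.** Neither input is in the documents; both are assumed. Let q be the proportion of recruits with a prior MI and k their 24-month AMI risk relative to the rest.

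Share recurrent = qk / (1 − q + qk)

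| q | k = 1 | k = 2 | k = 3 |
|---|---|---|---|
| 5% | 5.0% | 0.10/1.05 = 9.5% | 0.15/1.10 = 13.6% |
| 10% | 10.0% | 0.20/1.10 = 18.2% | 0.30/1.20 = 25.0% |
| 15% | 15.0% | 0.30/1.15 = 26.1% | 0.45/1.30 = 34.6% |

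For k between 2 and 3 the range is about 10 to 35%. With no excess risk (k = 1), the share equals q. If sites already turn such patients away, q is near zero and so is the share.

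**Step 4. Counts.** These depend on what is held fixed.

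- If 80 is the total of observed AMIs, the two ends of the range give 80 × 0.095 = 7.6 and 80 × 0.346 = 27.7 recurrent events.
- If 4% applies only to those without prior MI, among 2,340 × 0.85 = 1,989 participants, recurrences come on top of the first events. For q = 5%, k = 2: 1,989 × 0.95 × 0.04 = 75.6 first and 1,989 × 0.05 × 0.08 = 8.0 recurrent. For q = 15%, k = 3: 1,989 × 0.85 × 0.04 = 67.6 first and 1,989 × 0.15 × 0.12 = 35.8 recurrent.

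The shares are the same either way; the counts are not.

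**The case against.** **The article may be condensed.** It introduces the exclusions with the word include, gives examples of comorbidity, and sends detail to supplementary material. An item missing from a summary list may still be on the case report form. This has some force for the history lists. It has little for eligibility, which is printed as numbered criteria down to pregnancy and substance abuse. If a fuller protocol does exclude prior MI, the article misstates who is eligible and still needs correcting.

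**The intended population can be inferred.** A 10-year risk threshold suggests primary prevention, and the Discussion places participants before overt disease. But the article does not turn this into a rule, and recording prior stroke or TIA without excluding it suggests that established vascular disease is admitted.

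**First could mean first during follow-up.** The sentence in Outcomes permits that reading. The Discussion does not.

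**Stronger readings are not supported.** A reader might infer that recurrent infarctions will be counted as first events. No passage says so, and a panel holding a known history could reject a recurrence. A reader might also infer that prior MI cannot be identified at all. Electronic records, medication, echocardiographic wall motion and CCTA where indicated could reveal some cases. None is designated for that purpose, and records may not exist for participants found by community screening. What stands is that recurrences can be counted and cannot be reliably identified.

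**The harm has limits.** Medication is not a named Cox covariate, so a claim of biased medication hazard ratios would be speculative.

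**Conclusion.** The point holds in this form: freedom from prior MI, on which the primary endpoint depends, is neither a printed entry criterion nor a printed baseline item, and no described step confirms that an event is the participant's first. Followed as written, the text lets patients with an old infarction into the risk set and lets their events count.

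The absence from the criteria and from both history lists is read directly from the text. The size is not. The figure of about 10 to 35% rests wholly on an assumed prior-MI share of 5 to 15% and an assumed relative risk of 2 to 3, and it should be read as an illustration. Even a share near the low end matters where about 80 events have to support multivariable models and subgroup analyses. Confidence is lower that the actual case report form lacks these items, since it is not shown.

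**What to change.** 1. Add previous myocardial infarction, by history or medical record, as an exclusion criterion.
2. Add the participant's own prior MI, coronary revascularisation and established coronary disease to the baseline history, in the text and in the note to Table 1. Coronary disease without MI can then serve as a covariate or stratum.
3. Have the adjudication panel confirm for each event that it is the participant's first MI.
4. Restrict the primary analysis to participants free of MI at enrolment, and apply this to anyone already recruited. Establish their status now: reconstructing it only after an event would risk ascertaining it differently in cases and non-cases.

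Baseline echocardiography can support a sensitivity analysis that sets aside participants with findings suggesting an old infarction. It need not become a screening test, and the only ECG in the schedule is the 72-hour wearable recording, which the article does not present as a means of detecting old infarction.

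**Cost.** One eligibility line, three history questions and one adjudication item, with no new procedure. Some otherwise eligible patients are lost or set aside. Without replacement, and on the assumptions of 1,989 evaluable participants and a 4% rate, expected first events would be about 76, 72 or 68 if 5, 10 or 15% had a prior MI (1,989 × 0.95, 0.90 or 0.85 × 0.04). With replacement to the same number they stay at about 80.
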